# Design of the Pregnancy REmote MOnitoring II study (PREMOM II): a multicenter, randomized controlled trial of remote monitoring for gestational hypertensive disorders

**DOI:** 10.1186/s12884-020-03291-2

**Published:** 2020-10-15

**Keywords:** Remote monitoring, Gestational hypertensive disorders, Pre-eclampsia

## Abstract

**Background:**

Observational data from the retrospective, non-randomized Pregnancy REmote MOnitoring I (PREMOM I) study showed that remote monitoring (RM) may be beneficial for prenatal observation of women at risk for gestational hypertensive disorders (GHD) in terms of clinical outcomes, health economics, and stakeholder perceptions. PREMOM II is a prospective, randomized, multicenter follow-up study that was performed to explore these promising results.

**Methods:**

After providing written consent, 3922 pregnant women aged ≥18 years who are at increased risk of developing GHD will be randomized (1:1:1 ratio) to (a) conventional care (control group), (b) a patient self-monitoring group, and (c) a midwife-assisted RM group. The women in each group will be further divided (1:1 ratio) to evaluate the outcomes of targeted or non-targeted (conventional) antihypertensive medication. Women will be recruited in five hospitals in Flanders, Belgium: Ziekenhuis Oost-Limburg, Universitaire Ziekenhuis Antwerpen, Universitaire Ziekenhuis Leuven, AZ Sint Jan Brugge–Oostende, and AZ Sint Lucas Brugge. The primary outcomes are: (1) numbers and types of prenatal visits; (2) maternal outcomes; (3) neonatal outcomes; (4) the applicability and performance of RM; and (5) compliance with RM and self-monitoring. The secondary outcomes are: (1) cost-effectiveness and willingness to pay; (2) patient-reported outcome measures (PROMS) questionnaires on the experiences of the participants; and (3) the maternal and perinatal outcomes according to the type of antihypertensive medication. Demographic, and maternal and neonatal outcomes are collected from the patients’ electronic records. Blood pressure and compliance rate will be obtained from an online digital coordination platform for remote data handling. Information about the healthcare-related costs will be obtained from the National Coordination Committee of Belgian Health Insurance Companies (Intermutualistisch Agentschap). PROMS will be assessed using validated questionnaires.

**Discussion:**

To our knowledge, this is the first randomized trial comparing midwife-assisted RM and self-monitoring of prenatal blood pressure versus conventional management among women at increased risk of GHD. Positive results of this study may lead to a practical framework for caregivers, hospital management, and payers to introduce RM into the prenatal care programs of high-risk pregnancies.

**Trial registration:**

This study was registered on clinicaltrials.gov, identification number NCT04031430. Registered 24 July 2019, https://clinicaltrials.gov/ct2/show/NCT04031430?cond=premom+ii&draw=2&rank=1.

## Background

Worldwide, 5–8% of pregnant women develop gestational hypertensive disorders (GHD). In Flanders and Universitaire Ziekenhuis Brussels, the prevalence of GHD was 4.6% [1]. This means that ca. 3000 of 64,000 pregnancies in Flanders are complicated with this disorder each year. Of these, ca. 200 women (6.6%) delivered before the gestational age of 34 weeks because of GHD, 400 (13.3%) delivered between 34 and 37 weeks, and 2400 (80.1%) delivered after 37 weeks.

There are three main types of hypertension in pregnancy: essential/chronic hypertension (EH); gestational hypertension (GH); and pre-eclampsia (PE) [2]. EH is defined as a high blood pressure (> 140/90 mmHg, measured twice with an interval of 6 h), detected before conception or that develops during the first 20 weeks of gestation. This condition is associated with PE, intra-uterine growth restriction, and placental abruption [3–5]. GH is defined as elevated blood pressure (> 140/90 mmHg, measured twice with an interval of 6 h) that occurs after 20 weeks of gestation. Approximately 50% of all women diagnosed with GH will develop PE between 24 and 35 weeks of pregnancy [6]. PE involves hypertension accompanied by protein loss (> 300 mg/24 h) [2, 7], and is classified as early PE if it is diagnosed before 34 weeks of gestation, or as late PE if diagnosed after this time [8]. Recent definitions of PE also include maternal organ failure (e.g., renal insufficiency, liver disorders, neurological disorders, or hematological complications), utero placental dysfunction, or fetal growth retardation. If left untreated, PE is often fatal and, in low-income countries, it is a major cause of maternal and fetal mortality [9].

Women with an elevated risk of developing PE are more intensively followed up than women with an uncomplicated pregnancy. This results in an increased number of prenatal consultations and, when necessary, hospitalization to a prenatal ward for observation of the mother and the unborn child in order to regulate the medication schedule or to induce the delivery. Although randomized controlled trials of pregnant women at risk of developing GHD have shown that appropriate blood pressure measurement is an important component of prenatal care, standardized care processes that enable routine blood pressure measurement have not yet been introduced in clinical practice [10].

### Pregnancy REmote MOnitoring I study (PREMOM I)

By adding remote monitoring (RM) to the current prenatal follow-up program, it is possible to address the shortcoming described above. RM can be defined as the use of telecommunication technologies to assist the transmission of medical information between the patient and the caregiver [11]. This is a relatively new technique (it was used for the first time in the ‘90s) that facilitates home-based management of patients [12]. The PREMOM I study was set up in January 2015 as a collaboration in Belgium between Hasselt University, Ziekenhuis Oost-Limburg (ZOL; Genk), and seven other hospitals (AZ Vesalius, Tongeren; Heilig Hart Ziekenhuis, Mol; JESSA, Hasselt; Maria Ziekenhuis Noord Limburg, Overpelt; Sint Franciskusziekenhuis, Heusden; S. Trudo, Sint Truiden; and Ziekenhuis Maas & Kempen, Maasmechelen). Women who participated in the PREMOM I study received obstetric surveillance via a blood pressure monitor, an activity tracker, and a weight scale. They were asked to perform two blood pressure measurements each day (morning and evening), to wear the activity tracker continuously, and to register their weight once a week in the app. This information was to be recorded until the moment of their delivery or until they were admitted to the hospital. The data collected using these devices were transferred to an online dashboard developed by the Mobile Health Unit (Limburg Clinical Research Center, Hasselt University – ZOL – Jessa). Predefined alarm signals were developed. Alarm signals were communicated to the responsible obstetrician so that treatment options could be agreed with the midwife before the pregnant woman was contacted. The therapeutic interventions were in line with local treatment procedures. The workflow is summarized in Fig. 1.

**Fig. 1 Fig1:**
[figure not shown]
Workflow of PREMOM I

## RM for pregnancies complicated with GHD

### Observational studies and clinical outcomes

In the last few years, our research team has published two articles related to the PREMOM I project that demonstrated the benefit of RM for pregnant women at elevated risk of developing GHD [13, 14]. Both articles made comparisons between women who received RM and women who had an increased risk of developing GHD but did not participate in the PREMOM I study (conventional care, control group [CG]) based on a retrospective and observational design. In both studies, prenatal hospitalization to a prenatal ward (until the moment of delivery), diagnosis of PE, and number of inductions were reduced in the RM group compared with the CG. However, women in the RM group had significantly higher risks of developing GH and spontaneous start of the birth process compared with the CG. In the study conducted in 2015, the total number of neonatal hospitalizations to the neonatal intensive care unit (NICU) was lower in the RM group than in the CG group; these findings were not confirmed in the study conducted in 2015–2016. In the later study, the total number of prenatal visits was lower in the RM group than in the CG group; this difference was not apparent in the earlier study [13, 14].

To our knowledge, there have been no published articles describing the effects of RM for prenatal follow-up of women at risk for GHD since the prior PREMOM I studies. Nevertheless, numerous studies have investigated the feasibility of connected apps and digital devices for women at increased risk of pregnancy complications [15]. Many studies have shown that RM and home blood pressure measurements are a reliable and feasible manner to manage blood pressure in non-pregnant patients with hypertensive disorders [16–20]. Some studies have also compared usual care and RM for the management of postpartum hypertension, and concluded that RM is more successful than usual care in the follow-up and monitoring of blood pressure, and to detect warning signals [21, 22].

### Health economic considerations

The PREMOM I study also considered the health economics of RM for pregnant women in the 2015 and 2016 groups. RM enabled an average cost reduction for the Belgian National Health Care System of €740.39 per pregnancy (14.89%; 2015 data) up to €1950.37 per pregnancy (2015 + 2016 data). This cost saving was due to the reduction in prenatal visits, prenatal admissions, and neonatal admissions to the NICU [23, 24]. The savings were mostly related to neonatal care, particularly for neonates born at a gestational age of < 34 weeks, with a total cost reduction of €9123.16 per pregnancy in the RM group relative to the CG group. The cost reduction per pregnancy in the RM group versus the CG group was €225.86 for neonates born between 34 and 37 weeks and €35.93 for neonates born after 37 weeks. The finding that the main costs savings are driven by reduced neonatal care is not surprising since neonatal care is particularly intensive and is one of the most expensive forms of in-hospital care [25]. GHD-related neonatal morbidities include complications of prematurity, and the severity of prematurity is correlated with the cost of neonatal care [26]. Since the publication of those articles, we are not aware of additional health economic analyses of RM in pregnancy. Furthermore, there are few reports covering similar topics in non-pregnant patients.

### Experiences of the stakeholders

As part of the PREMOM I study, we examined the perceptions of midwives, obstetricians, and pregnant women, and found that the majority of healthcare professionals had none or little experience of RM before the study started [27]. However, after 1 year of using RM, the healthcare professionals felt that RM is an important tool in the prenatal follow-up of women at increased risk of developing GHD. They would also recommend it to their colleagues, and would roll-out this program to other centers in Belgium offering prenatal follow-up of pregnant women at increased risk of GHD. The pregnant women also reported a feeling of safety during their pregnancy and that they had no concerns about sharing their health status with the healthcare professionals. Most of the women wanted to be contacted, preferably by telephone, within 3–12 h after recording abnormal values. This implies the importance of 24/7 surveillance of the vital parameters of pregnant women at increased risk of developing GHD [27]. The compliance rate for blood pressure measurement was also high for morning (89.16%) and evening (89.00%) [27]. To our knowledge, there are no other articles describing the perceptions of stakeholders to RM of women at increased risk of developing GHD.

## Methods/design

### Aim of PREMOM II

While the PREMOM I study yielded positive and promising results, there are some aspects that warrant further investigation.
Increasing the external validity via a multicenter, randomized design.Performing thorough analyses of the factors that contribute to the benefit of RM for GHD, because blood pressure measurement itself does not have a specific effect. The research team assumes that the benefit of RM involves supervision from a midwife with knowledge of normal pregnancies and pathological events, and can anticipate potential clinical events when necessary. To investigate this, the timing and type of interventions will be meticulously registered.An uncontrolled form of RM will be built in, which totally relies on the motivation of the pregnant women. This group would be the patient self-monitoring (PSM) group, and will be included in PREMOM II.

PREMOM II is a prospective, multicenter, randomized controlled trial that aims to assess the benefit of RM for prenatal follow-up of pregnant women at increased risk of developing GHD.

### Study design

PREMOM II is a multicenter, randomized controlled trial that will be performed at five hospitals with their own prenatal wards between October 1, 2018 and March 30, 2022. The centers combined will perform more than 7000 deliveries per year. Eligible participants will be pregnant women ≥18 years old, who are able to understand oral and written information, with a minimum risk of 1/100 on the Fetal Medicine Foundation Tool (FMF) [28, 29]. By using the FMF tool will a risk assessment for the development of early PE be made, in which the following parameters are taken into account: (1) maternal characteristics; (2) medical history; (3) obstetric history; (4) information about the current pregnancy; (5) biophysical measurements. Women will be excluded if a congenital malformation is detected or if they do not have a smartphone.

The ethics committee at Universitair Ziekenhuis Antwerpen (UZA; Wilrijk) approved the study in July 2019 (Belgium Registration Number: BE300201938651). The local ethics committees at ZOL, Universiteit Ziekenhuis Leuven (Leuven), AZ Sint Jan (Bruges), and AZ Sint Lucas (Bruges) provided advice to the ethics committee at UZA before the study was approved.

General information about the study will be available at the antenatal care units at each site. All women who are pregnant for the first time, or who had a history of GHD in previous pregnancies, are given oral and written information about the study when they undergo their first trimester ultrasound examination. They will also be asked whether they want to be screened for the development of early PE. Women who are interested in participating the study are asked to give their informed consent and their risk will be calculated using the FMF tool. Pregnant women with a risk < 1/100 will not be randomized in the study, but will receive the standard follow-up in accordance with the local routine care. Pregnant women with a risk ≥1/100 will be randomized in one of the three study groups.

### Randomization

Figures 2 and 3 show the randomization process, trial flow and timeline table (according to SPIRIT). Randomization will be performed between 11 and 14 weeks of gestation, after the first trimester ultrasound examination. Using the Castor EDC web-based system, the women will be randomized to one of the three study groups at a 1:1:1 ratio by the study midwives, who also perform the inclusion in the PREMOM II study and the further RM follow-up (Figs. 2 and 3).

**Fig. 2 Fig2:**
[figure not shown]
Randomization process and study flow

**Fig. 3 Fig3:**
[figure not shown]
Timeline table – SPIRIT. G = gravidity; FMF = Fetal Medicine Foundation tool

#### Control group (CG)

Women in the CG will not be provided RM devices, and will instead receive standard prenatal care for women at increased risk of developing GHD.

#### Patient self-measurement (PSM) group

Women randomized to the PSM group will collect data, as per the RM group, but their data will not be sent to caregivers at the hospitals and interventions will be performed according to usual care. This group is included as a placebo control group for RM. The pregnant women in this group will be given a blood pressure monitor (BP5, iHealth, Paris, France) and will be asked to measure blood pressure twice daily. They will also record their body weight each week in the app. Only the pregnant women will be able to view the data recorded in the app. They will not be contacted by the study midwife when they aren’t compliant to the study protocol anymore. The compliance rate is a part of the study outcomes. All data will be stored for later use in data analyses.

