### Sample size calculations

Sample size calculations were performed by Censtat (Hasselt University, [name], [name]) to detect clinically meaningful differences between the midwife-assisted RM group and the CG in women with GHD, for two key factors (1) gestational age for neonates born before 34 weeks and (2) admission to the prenatal ward for neonates born after 34 weeks, based on previous work.
Gestational age for neonates born before 34 weeks: a difference of ≥10 days between the midwife-assisted RM group and the CG was observed in our pilot studies, and was used as a clinically relevant difference for the power calculation. Priority was given to this sample size calculation because each 1-day increase in gestational age at birth has a significant impact on the neonate’s short- and long-term outcomesAdmission to the prenatal ward of neonates born after 34 weeks: a proportional difference of 20% between the midwife-assisted RM group and the CG was considered clinically relevant. This outcome was expected to be most frequent in the PSM group, followed by the CG group, and less likely in the RM group.

The sample size calculations are based on summary statistics derived from our pilot study. A power of 80% and a significance level of 1.67% was used. A within-center variance of 6 (for gestational age) and a random intercept standard deviation of 0.0875 (for prenatal ward admission) was assumed. To obtain 80% power, we estimated that ≥168 GHD pregnancies with delivery before the gestational age of 34 weeks and ≥ 360 GHD pregnancies admitted to the prenatal ward after 34 weeks would need to be included in the study. At each center, the women will be equally divided into the three study groups.

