## Discussion

The PREMOM II study is the first RCT to evaluate the benefit of RM in the prenatal follow-up of pregnant women at increased risk of GHD. Our previous studies have already indicated that including RM in their care path will result in better pregnancy outcomes as well as a reduction in healthcare costs. Additionally, the stakeholders had positive views of RM. Although the results are promising, it is necessary to confirm them and to identify how RM provides these benefits. To answer these questions, we have designed PREMOM II as a multicenter RCT, in which the timing of interventions will be recorded and a PSM group will be included as a ‘placebo’ group.

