Our first hypothesis is that women in the midwife-assisted RM group will have lower numbers of prenatal consultations and unplanned hospital visits compared with the PSM group and the CG. We also believe that women in the PSM group will have the greatest healthcare consumption because their vital signs are not being reviewed by a healthcare professional and no one is able to provide them with specific advice or interpretations, so these women are likely to seek clinical support. Our second hypothesis is that the gestational outcomes will be improved in the midwife-assisted RM group as a consequence of fewer inductions, a greater number of spontaneous deliveries, fewer admissions to an NICU, and fewer diagnoses of PE relative to the CG. We expect that the outcomes of the CG and the PSM group will be the same because the women in these groups are not supervised by a healthcare worker. Related to the previous hypothesis, our next hypothesis is that midwife-assisted RM will not lead to an increase in costs to the healthcare system relative to conventional prenatal care in the CG, and that healthcare costs will be greater in the PSM group than in the CG. These expectations are based on the expected prenatal follow-up and the perinatal outcomes because interventions incur costs and negative gestational outcomes are expensive, and likely to exceed the cost of RM itself. Our penultimate hypothesis is that the number of interventions will be greatest in the midwife-assisted RM group, followed by the PSM group, and the CG. This assumption considers that the timely interventions will result in fewer evolutions of GHD to PE, leading to improved perinatal outcomes in the midwife-assisted RM group. This effect is expected to be smallest in the CG. We also think that appropriate adjustment of antihypertensive medications will result in improved outcomes. Our final hypothesis is that the midwife-assisted RM group will be associated with the most positive stakeholder perceptions, followed by the PSM group. The CG is expected to report the least positive perceptions.

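### For ward admission and healthcare use, the self-monitoring arm is called a placebo yet expected to exceed usual care, and the primary analysis does not make RM versus usual care decisive

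*Protocol article*

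**What the plan says.** All references are to the protocol article.

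- **Role of the arm.** The section on the PSM group states: "This group is included as a placebo control group for RM". The Discussion repeats that "a PSM group will be included as a ‘placebo’ group".
- **Expected behaviour of the arm.** Under Sample size calculations, on prenatal-ward admission: "This outcome was expected to be most frequent in the PSM group, followed by the CG group, and less likely in the RM group". In the Discussion: "We also believe that women in the PSM group will have the greatest healthcare consumption because their vital signs are not being reviewed". The reason given is that, with nobody to interpret their readings, these women are likely to turn to clinical services. The Discussion also predicts that "healthcare costs will be greater in the PSM group than in the CG".
- **Where these outcomes sit.** Consultations, prenatal-ward hospitalizations and their duration belong to the first primary outcome set (Primary outcome measures). Ward admission is one of the two outcomes used for sizing.
- **Sizing.** The sample size targets RM versus CG, with 80% power and a 1.67% significance level.
- **Primary analysis.** The end of Sample size calculations specifies two-sided Fisher's exact comparisons among the three groups at 0.05. It does not say which comparison supports a claim of RM benefit.

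**The concern.** A placebo arm supports a claim of benefit because it is expected to leave the outcome where no intervention would leave it. By the plan's own account PSM does not do that for ward admission and healthcare use: unreviewed readings are expected to drive use above conventional care. On these outcomes PSM is an active comparator expected to do worse than usual care.

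This would matter little if the analysis rested on RM versus CG. As written it rests on comparisons among three groups, one of which is expected to be displaced upwards. A significant three-group test, or RM lower than PSM, could then be read as remote monitoring reducing admissions when RM and current care are equal. The trial is meant to persuade caregivers, hospital administrators and government to add RM to current care, so RM versus current care is the comparison they need.

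**Working it through.** **Inputs**

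- Women for the ward-admission outcome: 360 (Sample size calculations). With 1:1:1 allocation, 360 / 3 = 120 per arm.
- Admission rate: 42% (Sample size calculations, given as a minimum among women with GHD). Using it as the CG rate is an assumption.
- RM-CG difference used for sizing: 20%, read here as percentage points (an assumption). Power 80%, two-sided level 1.67%, which is about 0.05 / 3.
- PSM excess over CG: **not stated**. Range tried: 0, 5, 10 and 20 points.

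**Step 1: reproduce the plan's figure.** For two proportions,

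n = [z₁√(2p̄(1−p̄)) + z₂√(p₁(1−p₁)+p₂(1−p₂))]² / (p₁−p₂)²

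Take p₁ = 0.42, p₂ = 0.22, p̄ = 0.32, z₁ = 2.393 (two-sided 1.67%) and z₂ = 0.842 (80% power). This gives n = 112.5, so 113 per arm and 339 in total. With the continuity correction, (n/4)[1 + √(1 + 4/(n × 0.20))]² = 122.3, so 123 per arm and 369 in total, within 3% of 360. The arm rates are not stated and the centre effect is ignored, so this shows that 360 fits an RM-CG sizing at 1.67%; it does not show how 360 was obtained.

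**Step 2: set RM equal to CG and let only PSM differ.** Put RM = CG = 0.42 and PSM = 0.42 + e, with n = 120 per arm. The three-group test is approximated by a chi-square test on 2 df, with noncentrality

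λ = n[2(e/3)² + (2e/3)²] / [p̄(1−p̄)], where p̄ = 0.42 + e/3.

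- e = 0.05: p̄ = 0.4367, λ = 0.81, power about 12%
- e = 0.10: p̄ = 0.4533, λ = 3.23, power about 34%
- e = 0.20: p̄ = 0.4867, λ = 12.81, power about 90%

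**Step 3: simulation of the same setting** (20,000 trials for the three-group test, 4,000 for the pairwise Fisher tests, all at 0.05):

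| PSM excess (points) | Three-group test significant | RM significantly below PSM | RM vs CG significant |
|---|---|---|---|
| 0 | 4.9% | 1.8% | 3.3% |
| 5 | 11.8% | 9.6% | 3.9% |
| 10 | 34.9% | 29.2% | 3.6% |
| 20 | 91.2% | 84.0% | 3.7% |

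The three-group column agrees with step 2. Only RM versus CG is unaffected by what PSM does. About half of its significant results favour RM (roughly 2%).

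**Step 4: larger arms.** With 3922 / 3 = 1307 per arm, a 5-point excess gives 76.0% for the three-group test and 71.1% for RM below PSM. RM versus CG stays between 3.6% and 5.1% over the whole range of excess. This is an upper illustration, because the 42% refers to women with GHD and not to everyone randomized.

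**The case against.** A good deal can be said for the plan, and most of it stands as a limit on the point.

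- **The first hypothesis.** A reader might infer that RM could meet it on the back of a poor PSM arm. It could not: RM is expected to have fewer visits than PSM and CG alike, so a trial with RM equal to CG fails it.
- **Cost.** A reader might infer that the reimbursement case is distorted. The Health economics section already defines the incremental cost of RM as RM against CG.
- **Apparent self-contradiction.** The sentence "We expect that the outcomes of the CG and the PSM group will be the same" might be set against the predicted PSM excess. It follows the hypothesis on inductions, spontaneous deliveries, NICU admissions and PE diagnoses, so it concerns gestational outcomes. The ranking of RM above PSM above CG concerns the number of interventions. Neither contradicts the healthcare-use prediction.
- **PSM has a purpose.** The aims section attributes the benefit of RM to midwife supervision, and an arm that measures without supervision helps isolate it. RM acts on gaps of more than 48 hours, whereas for PSM women "They will not be contacted by the study midwife when they aren’t compliant to the study protocol anymore". That is part of the supervision being studied, not a fault in the comparison.
- **An unseen SAP.** Contrast ordering is often left to the SAP, and the plural for comparisons, with 1.67% close to 0.05 / 3, may point to three pairwise tests.

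The last argument does not remove the point. The article does not leave the primary analysis open: it names a test, a set of groups and a level, and both the contrast and the level differ from those used for sizing. If the comparisons are pairwise, RM versus PSM becomes one of three tests at 0.05 with none marked as decisive, and the third column of the table applies.

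**Conclusion.** The point holds for prenatal-ward admission and healthcare use. On these outcomes the plan labels PSM a placebo, predicts that it will exceed conventional care, and states a primary analysis in which that excess alone can produce significance. With RM equal to CG at 42% and 120 per arm, this happens in about 12%, 35% or 91% of trials for an assumed PSM excess of 5, 10 or 20 points. RM versus CG stays at 3-5%.

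The direction of the excess is the plan's own prediction; its size is assumed. The 20 points in the last scenario is borrowed from the RM-CG sizing difference and is not a forecast for PSM. The percentages should not be read as type I error rates of the three-group test, because in these scenarios PSM truly differs. They show how often a correct finding about PSM would be open to misreading as a finding about RM.

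The point does not extend to gestational outcomes, where PSM and CG are expected to agree, or to the incremental-cost analysis. It is not an argument against having the PSM arm. The valid contrast is already in the design and was the one used for sizing; the stated primary analysis does not make it decisive.

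**What to change.** In the primary-analysis paragraph at the end of Sample size calculations:

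1. State that a claim of RM benefit over current care rests on RM versus CG, tested at the level used for sizing (1.67%).
2. Report RM versus PSM as the added effect of midwife supervision, including the action on gaps of more than 48 hours.
3. Report PSM versus CG as the effect of self-monitoring alone, which tests the plan's prediction that it raises healthcare use.

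In the PSM group section and the Discussion, describe PSM as an active self-monitoring comparator instead of a placebo.

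The change is to wording only: arms, sample size and data collection are unaffected. The price is that a significant three-group or RM-PSM result can no longer be presented on its own as evidence of RM benefit.
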